### Interventions

The intervention will consist of either an MAD (n=22, SomnoMed Avant, Somnomed UK) with the dental sleep medicine department or CPAP (n=22, S8/S9, ResMed, Sydney, Australia) with the sleep medicine department.

### Titration of devices and repeat assessment

The CPAP mask will be delivered as standard of care and, therefore, may be different for each patient. The same CPAP therapy allocated to the participant will be used in the follow-up investigation. Some adjustment of the devices may be needed to ensure comfort and efficacy of the device. This will be done as routine care and scheduled as needed.

Following successful titration for each device and a 3-week customisation period, the 24-hour impedance monitoring and home sleep study will be repeated. As at visit 1, participants will be asked to cease their PPIs, H2-receptor antagonists or antacids. A dental examination will be carried out by the research dentist to ensure there have been no changes in the oral cavity. Participants will be asked to review their diet diary from the day they first did the test and repeat what they ate or drank as closely as possible for the day. That afternoon the participant will attend the oesophageal physiology laboratory. Participants will repeat the RSI questionnaire, ESS questionnaire, Leicester Cough Questionnaire and a QoL questionnaire. The pH impedance testing and Watch-PAT testing will be repeated as described above. Compliance levels for the MAD and CPAP therapy on the same night will be obtained.

On returning the next day to have their pH probe removed and to return the Watch-PAT, participants will be asked to complete a questionnaire about their views in taking part in the study.

### Blinding

This is a single-blinded study. The statistician is the only member of the team who can be blinded to the allocation. The database has been created such that the intervention is not known to the statistician when performing the analysis. The patient and clinician cannot be blinded to the group allocation due to the nature of the therapeutic devices used. However, the objective, computer-generated clinical measurement outcome in for the definitive trial is less likely to be subject to bias.

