Following placement of the catheter, participants will be invited for their home sleep study. A type 3 sleep study device, the WatchPAT 200 (WP200; Itamar Medical, Caesarea, Israel) will be given in addition to comprehensive instructions on how to perform a home sleep study. A 24-hour number for technical support will be provided to the patient. After their overnight sleep study, they will return the following day to the gastroenterology department for removal of the probe and return of the WatchPAT.

The gastroenterology data will be captured by ZepHrTM recording device and data will be analysed using the BioVIEW Analysis software (V.5.7.1.0). The sleep study data will be analysed by a qualified sleep technician.

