### Randomisation procedures

Participants who meet the inclusion/exclusion criteria will be allocated 1:1 using fixed-block randomisation by the purpose-built computer-generated randomisation service provided by King’s Clinical Trials Unit (KCTU) to either the CPAP (n=22) or the MAD (n=22) arm. Once the participant identifier is entered into the system, an e-mail will be sent to the principal investigators and trial manager informing them of the allocation.

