### Data collection and management

Clinical, demographic and questionnaire data will be collected on case report forms. Clinical data from manometry, impedance testing and sleep study will be obtained through patient electronic records and recorded on case report forms. Paper forms will be used, and data will be recorded on electronic case report forms held in a database using MACRO V.4.0 (Infermed) and maintained by the KCTU. Data checks will be performed by the trial manager and the trial statistician. The statistician and principal investigator will have access to the full trial data set at the end of the trial.

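### The statement that only the statistician can be blinded is not justified for whoever analyses the follow-up pH recording, and masked analysis of that recording is not provided for

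*Protocol article*

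**What the plan says.** The Blinding section of the protocol article calls the trial single-blinded and says "The statistician is the only member of the team who can be blinded to the allocation". It then gives a reason: "The patient and clinician cannot be blinded to the group allocation due to the nature of the therapeutic devices used". As mitigation it adds that the objective, "computer-generated clinical measurement outcome in for the definitive trial is less likely to be subject to bias".

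Under Study screening procedures, the handling of the reflux recording is described as follows: "The gastroenterology data will be captured by ZepHrTM recording device and data will be analysed using the BioVIEW Analysis software (V.5.7.1.0"). No operator is named. The section on titration and repeat assessment says that the follow-up test repeats this procedure with the allocated device in use.

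Randomisation procedures says that after allocation "an e-mail will be sent to the principal investigators and trial manager informing them of the allocation". Data collection and management says: "Clinical data from manometry, impedance testing and sleep study will be obtained through patient electronic records and recorded on case report forms".

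Under Outcomes, the primary clinical outcome is the change in percentage acid contact time below pH 4, taken from the night part of the 24-hour recording. Its stated purpose is to signal efficacy and inform the power calculation of the definitive trial.

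**The concern.** The Blinding section makes a positive claim about what is possible. It does not merely leave reader masking unmentioned. The claim is wider than the reason offered for it: a device worn by the patient explains why patient and treating clinician know the arm, but not why a person analysing a stored file must know it.

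This matters because masking the statistician acts late. By the time the statistician sees the data, the acid contact time has already been derived, placed in the patient record and copied to the case report form. If that derivation leaves any room for judgement, and the judgement differs by arm, the error sits inside the recorded value and a blinded analysis cannot remove it. The affected quantity is the one clinical estimate that the trial carries forward.

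**Working it through.** The point rests mainly on setting the sections side by side. Arithmetic serves only to show what does not change and what this trial could not detect.

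**Whom the stated reason covers.** The Blinding section applies the nature of the devices to the patient and the clinician. The analyst of the recordings appears in neither group, and no other reason is given.

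**When analysis happens.** Study screening procedures has the signal captured on a recorder and analysed in software. The probe is removed the day after insertion. Analysis therefore follows capture, and nothing described in it uses the identity of the allocated device.

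**Who is told the arm.** The allocation e-mail in Randomisation procedures goes to the principal investigators and the trial manager. No analyst is listed as a recipient.

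**How the value reaches the database.** Data collection and management routes it through patient electronic records to the case report form, with no masking step stated.

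**Where judgement could enter.** The outcome uses night data from a 24-hour trace, so some rule has to delimit the night. The article does not say whether that rule is automatic, fixed in advance or set by the analyst.

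**The plan's own figures (Sample size).** Inputs: margin 4.15, SD 10.8, power 90%, one-sided alpha 2.5%.
- Normal approximation per arm: n = 2 × (1.96 + 1.2816)² × 10.8² / 4.15² = 142.3, so 143 per arm and 286 in total.
- With the noncentral t distribution: 144 per arm and 288 in total (power 0.901), the stated figure.
- 9% × 288 = 25.9, so 26. Then 26 / (1 − 0.40) = 43.3, so 44.

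The chain reproduces. Masked reading alters none of it.

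**What this trial could detect.** The half-width of the 95% CI for a mean difference is t × SD × √(2/n). With SD 10.8:
- 13 per arm (26 completers): 2.064 × 10.8 × √(2/13) = 8.7 points.
- 22 per arm (all randomised): 2.018 × 10.8 × √(2/22) = 6.6 points.

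**Sensitivity to an assumed shift.** The documents give no size for reader error. Suppose the reading shifts the between-arm mean difference by b points against MAD, and the same reading practice is carried into a 288-person trial. Power is then Φ((4.15 − b) / (10.8 × √(2/144)) − 1.96), where the denominator is 1.273.

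| Assumed b | b as share of margin | Power |
|---|---|---|
| 0 | 0% | 90% |
| 0.5 | 12% | 82% |
| 1 | 24% | 70% |
| 2 | 48% | 39% |

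These rows are hypothetical and are not estimates of bias in this trial. The margin is expressed in per cent total acid, whereas the outcome is nocturnal, so the scale is only indicative. The table shows that shifts of this order would affect the definitive design, yet each is far inside the half-widths above and would go unnoticed here. A shift of this kind has to be prevented by procedure, because these data could not reveal it.

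**The case against.** The strongest reply is that the outcome is machine-derived. The article names no manual editing, artefact removal or window setting, so a reader who infers that the acid contact time is materially biased goes beyond the text. That stands: the amount of human judgement in the software analysis is undocumented, and the bias may be negligible. Only error that differs between arms would matter; error common to both cancels in the difference.

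A reader might also infer that the sleep recordings are exposed, since "The sleep study data will be analysed by a qualified sleep technician". The documents do not support extending the point to them. The Discussion says AHI serves solely as an inclusion criterion, no listed outcome is a sleep-study score, and the sleep reading that decides eligibility precedes randomisation.

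Third, masking may be imperfect. The Discussion describes placing and taping the catheter to keep the CPAP mask seal, so laboratory staff may learn the arm. Electronic records may show it too. The article does not say whether the pH analyst is separate from the unblinded clinicians. This stands as a limit on how complete masking would be. It does not show that masking is impossible or costly, and the article does not offer it as a reason.

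Fourth, a condensed article may leave file handling to the full protocol. That would answer a complaint about silence. Here the article asserts that nobody else can be blinded, and a full protocol that provided for a masked analyst would contradict that sentence.

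Finally, the stakes are limited. The primary outcomes are screening, randomisation and completion percentages, which reader masking cannot affect, and the Statistical analysis section plans estimates without hypothesis tests.

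**Conclusion.** The claim that only the statistician can be blinded is unsupported for one role: whoever analyses the follow-up pH-impedance recording. The gap concerns the change in nocturnal acid contact time and, through it, the estimate meant for the definitive power calculation. The feasibility outcomes and all stated sample sizes are untouched.

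The size of any bias is unknown and possibly small. The documents do not support the stronger conclusion that the outcome is biased, nor that masking is certain to succeed with present staff. That masking is feasible is a reasonable inference from offline analysis of stored files and from the short list of people told the allocation; it is not a documented fact.

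The weight is minor to moderate. The case for acting is that the protection is cheap, and that a feasibility trial is a sensible place to learn whether masked reading works before the multicentre trial that the Discussion foresees.

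**What to change.** Amend the Blinding section, with a matching line where the pH analysis is described, to say that:

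- follow-up pH-impedance files are exported under a study code that does not show the arm;
- they are analysed by the reader who already does this work, without access to allocation and, where possible, not by the person who fitted the catheter at follow-up;
- the night window is fixed by the same rule in both arms;
- the derived values are locked before they are linked to arm.

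If this cannot be done, replace the absolute statement with the reason why the analyst cannot be masked.

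The cost is a little file coding and a short delay before results are linked. No extra reader, procedure or participant is needed. Masking may remain incomplete where the reader met the patient at follow-up, and the report should say so.

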### Data collection and management

Clinical, demographic and questionnaire data will be collected on case report forms. Clinical data from manometry, impedance testing and sleep study will be obtained through patient electronic records and recorded on case report forms. Paper forms will be used, and data will be recorded on electronic case report forms held in a database using MACRO V.4.0 (Infermed) and maintained by the KCTU. Data checks will be performed by the trial manager and the trial statistician. The statistician and principal investigator will have access to the full trial data set at the end of the trial.

### Qualitative interviews

To enhance our understanding of acceptability of recruitment processes, screening procedures and of taking part in the trial, we will conduct telephone interviews with participants (approximately n=16) over the course of the trial. We will use a sampling matrix to include patients who elected not to take part, eligible patients who were screened but did not take part in the trial, patients who could not tolerate the device or discontinued the trial for other reasons, and those who completed the trial.

Using the Theoretical Framework of Acceptability^29^ to underpin the interview guide, participants will be asked about different domains of acceptability (eg, affective attitude, burden, coherence, perceived effectiveness) for each element of the trial, including recruitment, randomisation, appointments and procedures, use of devices. Participants will also be asked about barriers to trial participation, potential improvements and how to create advocacy for the trial among stakeholders. Participants will receive an additional £25 if they take part in this 25 min interview. The interviews will be audio-recorded, anonymised and professionally transcribed verbatim, in preparation for framework analysis^30^ whereby a thematic framework is developed and applied to the transcripts, allowing systematic analysis and interpretation of the qualitative data. Data will be managed in NVivo.

### Health economic measures

During the feasibility phase, the best way of collecting relevant service costs, and patient borne costs, from both an NHS and a wider societal perspective will be investigated to inform a future full trial context.^31–33^ We will consider to what extent this intervention constitutes a complex intervention, drawing on guidance from the UK Medical Research Council for the guidance for complex interventions.^34^ In the context of the patient, we will pilot the (EQ-5D-5L),^22^ ICECAP-A^23 24^ and the SWEMWBS,^25^ which could be used in a full RCT to calculate cost per QALYs and wider outcomes. We will determine if these are sufficiently sensitive to measure change in the patient group. We will also determine the appropriate deterministic sensitivity analysis in a full economic analysis in this patient group. We will pay attention to distributive cost-effectiveness analysis opportunities in a full trial.^35^

Our base-case analysis will explore the likely total costs (intervention costs and medical costs) and outcomes (health resource service use and health-related quality of life) of using MADs compared with CPAP therapy in people with OSA who have nocturnal GORD in a future full trial. We will also explore if these outcome measures accurately reflect the conditions of the patients.

We will write a report to the funder and papers for peer-review publication following the Consolidated Health Economic Evaluation Reporting Standards statement^36^ and the Assessment of the Validation Status of Health-Economic Decision Model.^37^ The health economic feasibility study will be reported in accordance with the Consolidated Standards of Reporting Trials extension.^38^

A full schedule of events is given in online supplemental table 1 and the patient flow diagram with feasibility outcomes is illustrated in figure 1.

10.1136/bmjopen-2023-076661.supp1Supplementary data

**Figure 1 F1:**
[figure not shown]
Study flowchart showing feasibility outcomes. Dx, Diagnosis; Rx, Prescription; CPAP, continual positive airway pressure; ESS, Epworth Sleepiness Scale; GORD, gastro-oesophageal reflux disease; OSA, obstructive sleep apnoea; RDQ, Reflux Disease Questionnaire; RSI, Reflux Symptom Index; PAT, Peripheral Arterial Tonometry; VAS, Visual Analog Scale; QoL, Quality of Life.

### Adverse events

All adverse events (AEs) will be recorded from the time of randomisation. AEs will be classified according to severity and whether related to the study intervention. All serious AEs will be reported immediately by the chief investigator and, no later than 24 hours, to the research & development office (sponsor) and main research ethics committee.

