### Study screening procedures

Following written informed consent by a trained member of the research team, participants will undergo assessments at a screening visit to ensure eligibility is met. Participants will be informed that PPIs will need to be stopped 7 days prior and H2-receptor antagonists or antacids 48 hours prior to this visit. Participants will complete an RSI questionnaire, ESS questionnaire, Leicester Cough Questionnaire and several QoL questionnaires. A full dental examination will be conducted to ensure that participants are dentally fit to wear an MAD if allocated to this intervention. For the gastroenterology assessment, the patient will initially need to undergo high-resolution manometry (HRM). Following local analgesia of the nares the catheter will be introduced transnasally and the patient instructed to drink water through a straw while the HRM catheter is advanced to the stomach. The HRM catheter depth will be adjusted to ensure manometric visual of the upper oesophageal sphincter, the gastro-oesophageal junction and gastric pressures. Ten single swallows of 5 mL will be performed with each being 20 s apart. Each 5 mL water swallow will be assessed in accordance with Chicago classification (V.3) using Manoview software (V.3) (Sierra Scientific Instruments). The HRM catheter will then be removed.

Patients will then undergo reflux monitoring using Sandhill Scientific multichannel impedance pH catheters (ZANBG-44), which are inserted transnasally after applying local anaesthesia (xylocaine). The dual pH sensors of the catheter will be positioned 5 cm below and above the manometric LOS. The impedance sensors will be positioned above the LOS by 3 cm, 5 cm, 9 cm, 15 cm and 19 cm. The data will be captured by ZepHrTM recording device.

For the 24 hours while the probe is inserted, the participant will be asked to complete a food diary as food and drink will impact on their reflux. Stopping reflux medication and the food diary are part of standard care for this procedure.

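### Adverse event recording starts at randomisation, after the consented invasive screening, so non-serious screening events go unrecorded and screen failures have no adverse event record

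*Protocol article*

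**What the plan says.** The Adverse events section fixes the start of recording: "All adverse events (AEs) will be recorded from the time of randomisation". It adds that "AEs will be classified according to severity and whether related to the study intervention"; study procedures are not named as a possible cause. On serious events it says "All serious AEs will be reported immediately by the chief investigator and, no later than 24 hours", to the sponsor's office and the ethics committee, with no start time of its own.

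The section on study screening procedures sets out what comes earlier. "Following written informed consent by a trained member of the research team, participants will undergo assessments at a screening visit". Participants are told that "PPIs will need to be stopped 7 days prior and H2-receptor antagonists or antacids 48 hours prior to this visit". At the visit a transnasal manometry catheter is passed and removed, and a transnasal pH-impedance catheter is then placed and left in for 24 hours, including a night at home with the sleep-study device. "After their overnight sleep study, they will return the following day to the gastroenterology department for removal of the probe".

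Under Inclusion/exclusion criteria, entry requires an acid exposure time above 6% over 24 hours, and under Randomisation procedures only participants who meet the criteria are allocated. The section on titration and repeat assessment then has reflux medication stopped again and the pH-impedance and sleep tests done once more with the allocated device.

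**The concern.** The eligibility rule forces the order of events. Nobody can be randomised without a completed 24-hour catheter result, so every first catheter study lies before the point at which recording begins. For someone who turns out to be ineligible, or who declines after screening, recording never begins.

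This matters more here than in many trials. The Introduction makes tolerance of the trial part of the overall aim, and says it is unknown whether patients will wear several devices and tests while trying to sleep. Events caused by the testing are therefore information that the definitive trial needs. The stated window keeps mainly the second catheter study, in people who have already been through one. Those who could not undergo the tests are excluded by the eligibility criteria, and so never enter the window. The record of what testing does to patients would therefore rest on a group selected for having coped with it.

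**Working it through.** **Inputs from the protocol article**
- Randomised: 44; attrition allowed for: 40%; evaluable target: 26, being about 9% of a definitive sample of 288 (Sample size).
- One pH-impedance catheter study per patient before randomisation, because eligibility depends on it (Inclusion/exclusion criteria; Study screening procedures).
- One repeat pH-impedance study after randomisation (Titration of devices and repeat assessment).

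**Input not in the article**
- The share *e* of catheterised patients who go on to be randomised. It is varied below as an assumption.

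**The plan's own figure**
- 0.09 × 288 = 25.9, rounded to 26.
- 26 / (1 − 0.40) = 43.3, rounded up to 44. The stated number reproduces.

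**Share of catheter studies outside the recording window**

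With attrition *a* before the repeat test:

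share = (44/*e*) / (44/*e* + 44 × (1 − *a*))

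Using only the article's figures, with no screen failures (*e* = 1):
- *a* = 0: 44 / (44 + 44) = 44/88 = 50%.
- *a* = 0.40: 44 × 0.60 = 26.4 repeat studies; 44 / (44 + 26.4) = 44/70.4 = 62.5%.

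These are floors for each attrition rate, because every catheterised patient who is not randomised adds a study outside the window and none inside. With assumed values of *e*:

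| *e* (assumed) | Catheter studies before randomisation | Share outside, no attrition | Share outside, 40% attrition |
|---|---|---|---|
| 100% | 44 | 50% | 62.5% |
| 75% | 59 | 57% | 69% |
| 50% | 88 | 67% | 77% |
| 25% | 176 | 80% | 87% |

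**Manometry**

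The repeat-assessment text names the pH-impedance and sleep tests but not manometry. If manometry is done only at screening, all of it falls outside the window. The article does not settle this.

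**Serious events**

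Read alone, the serious-event sentence covers all serious events. Read after the sentence that starts recording at randomisation, it could be taken to cover only those from randomisation on. The wording supports either reading.

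**The case against.** **The later exposure is captured.** The catheter test and medication withdrawal are repeated inside the window, with the therapy device worn as well. This stands, and it means that the loss is partial. It does not help those who are never randomised or who drop out before the repeat.

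**Tolerance is measured in other ways.** The feasibility percentages follow patients from screening to completion, and about 16 interviews cover acceptability, including of screening. This stands in part: tolerance of testing would not go unmeasured. But the interviews are few, their sampling matrix does not list patients found ineligible at screening, and neither source is a record of adverse events.

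**A start at randomisation suits a comparison of two devices.** It does, and no feasibility percentage, clinical estimate, interval or sample size changes. But the comparison by arm would be kept if the earlier period were recorded and reported separately.

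**Standard care.** The article says that stopping reflux medication and keeping a food diary are standard for this procedure. It does not say that the procedure is routine for these patients, who are referred for sleep apnoea; it presents the work-up as a consented screening step of the trial.

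**The full protocol may cover it.** The full protocol and the supplementary schedule of events are not shown and might deal with screening events. If they do, the sentence in the article still states a different rule and needs correcting.

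**Conclusion.** The point holds for non-serious events at screening. Under the stated rule they are not recorded, and patients who fail screening have no adverse event record. At least 50% of catheter studies fall outside the window, and about 62% at the plan's own attrition rate. Both figures assume one study before and one after randomisation and no catheterised screen failures; any such failure raises them.

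A reader might infer more than the article supports:
- *That most procedure-related harm is lost.* The article gives no harm rates. The shares count procedures and would carry over to harm only if each study had a similar risk.
- *That serious events at screening go unreported.* That sentence has no start time, so they are not expressly excluded. The text is unclear and should be settled.
- *A headcount of patients tested without a safety record.* This needs a screening yield that the article does not give. In addition, not everyone screened need be catheterised: a dental examination is described before the gastroenterology assessment, and a patient may fail there.
- *That medication is always stopped after consent.* Consent is placed before the screening assessments, but withdrawal starts up to 7 days before the visit, and the order of the two is not fixed.

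The remaining point concerns safety capture and the tolerance aim. It is worth correcting, but it does not threaten the trial's estimates.

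**What to change.** Change the Adverse events section in three ways.

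1. Start recording of both adverse events and serious adverse events at written consent, or at medication withdrawal requested by the study if that comes earlier, and say explicitly that serious-event reporting uses the same start.
2. Assess relatedness to study procedures (medication withdrawal, manometry, catheter, overnight monitoring) as well as to the allocated device.
3. Report two periods: consent to randomisation for all screened patients, with the number who had each procedure as denominator, and from randomisation onwards by arm.

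The cost is an adverse event form at the screening visit and slightly more data entry. Patients already return the next day for probe removal, which gives a natural time to complete it. No treatment, procedure or sample size changes. Events not recorded at the time cannot be reliably recovered later.
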